**Fig. 2 fig2:**
[figure not shown]
Hypothetical form of the results for control group (green) and intervention group (blue). The figure captures the intended change for underweight and overweight children and the intended no change for children with weight in the normal range. (For interpretation of the references to colour in this figure legend, the reader is referred to the Web version of this article.)

As Fig. 2 suggests, the expected findings depend on the initial distribution of WAZ. An effect of the intervention may show as a main effect if the participants fall mainly at one end of the WAZ distribution, an interaction between Treatment and Baseline if baseline WAZ extends from one end of the WAZ distribution to 0, or an interaction between the cubed Baseline term and Treatment if baseline WAZ spans the entire WAZ distribution.

Thus, to analyze the change in WAZ, we will first identify the best fitting regression model, starting with [17]. The independent variable Treatment will be coded 0 (control - standard care arm) and 1 (intervention arm). Interaction and cubic terms will be then added, at each step assessing if a more complex model is warranted by the data, based on adjusted R-squared [18] shows the most complex model we expect to assess. We will report the results from the best fitting model.(1)$${WAZpost\;∼\;b}_{0+b1*Treatment+b2*WAZpre}$$(2)$$WAZpost\;∼\;b0+b1*Treatment+b2*WAZpre+b3*Treatment*WAZpre+b4*WAZpre^{3}+b5*Treatment*WAZpre^{3}$$

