### Sample size calculation

4.1

Sample size calculations are based on assuming that 1) is the best fitting model. While it is desirable to base sample size on the most complex model used in the analyses, given that 1) it is unclear which model will show best fit to the data, and 2) estimates of sample size for regression models including interactions require understanding of the correlations between the variables, an understanding that we currently do not have, this approach was deemed warranted.

Sample size calculations were conducted in G*Power 3.1 1 Fig. 3 shows the sample size calculations assuming that 1) the effect of the intervention will be small to medium, and 2) a two-sided significance test.

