**Fig. 3 fig3:**
[figure not shown]
Required sample size expecting small-to-medium effect of the intervention.

We decided to aim for a total sample of 100 participants, which will allow us to detect effects as small as f2 = 0.075 with power of 0.8. Importantly, this sample size also allows us to have reasonable confidence in detecting small-to-medium effects (e.g., f2 = 0.1) assuming a drop out rate as large as 30 % (i.e., final n = 70), which is important for per-protocol analyses.

Secondary analyses will explore nutrition's impact on health and wellbeing in children with CP, focusing on four key areas:1.Anthropometric Measures: Beyond the primary measure of Weight for Age Z-score (WAZ), we will use BMI, skin fold thickness, and mid-upper arm circumference, using age-standardized z scores, to assess the robustness of our conclusions about the effectiveness of the intervention across anthropometric indicators of nutritional status.2.Biochemical Indicators: Analyzing Vitamin D and iron levels to identify changes in nutritional deficiencies between intervention and control groups.3.Healthcare Utilization: We'll assess health indexes such as bedridden days, emergency visits, infections, hospitalizations, and impact on regular activities and family life, comparing improvements between the intervention and control groups.4.Behavior and Quality of Life: Investigating changes in child behavioral functioning and family quality of life to determine if the intervention group shows greater improvements compared to the control group.

These analyses will deepen our understanding of the nutritional intervention's broader impacts on children with CP and their families.

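### The primary WAZ model is chosen on the trial's own outcome data by adjusted R-squared and no single primary test is fixed, so the false-positive rate is above nominal

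*Protocol article*

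**What the plan says.** WAZ is the primary outcome: section 4.1 lists the secondary measures as "Beyond the primary measure of Weight for Age Z-score (WAZ"). Section 4 (Planned analyses, text around Fig. 2) sets three rules for it.

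- **Selection.** Model (1) regresses final WAZ on Treatment and baseline WAZ. Further terms are added, "at each step assessing if a more complex model is warranted by the data, based on adjusted R-squared". Model (2), the most complex, adds Treatment x WAZpre, WAZpre cubed and Treatment x WAZpre cubed.
- **Reporting.** "We will report the results from the best fitting model".
- **Interpretation.** Three forms of effect are allowed, each tied to the spread of baseline values. The first is the simplest: "An effect of the intervention may show as a main effect if the participants fall mainly at one end of the WAZ distribution". The second is a linear Treatment-by-baseline term, for baseline values that run from one tail as far as zero. The third is a cubic Treatment-by-baseline term, for values that cover both tails.

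Section 4.1 adds "Sample size calculations are based on assuming that 1) is the best fitting model" and "2) a two-sided significance test". It states no alpha. Section 5 (Data management) has the analyst work on neutral group codes until the primary analysis is complete.

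**The concern.** Two of the added terms, b3 and b5, are treatment terms. Whether they enter the model depends on final WAZ and the group codes, and they are then tested on those same data. Any of b1, b3 and b5 may be read as the effect, and nothing says which one carries the primary conclusion or how the selection is allowed for. The primary p-value then lacks its nominal error rate, and the standard errors ignore the selection. A significant result could not be taken as confirmatory, although the trial is meant to inform clinical guidelines. The term finally tested may also differ from the one on which the trial was sized.

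**Working it through.** **The plan's own figure.** The plan gives no error rate for the procedure, only power: f2 = 0.075, N = 100, power 0.80. With a noncentral F test of one coefficient (noncentrality f2 x N = 0.075 x 100 = 7.5, 97 residual df, two-sided 5%) power is 0.774. Power of 0.80 needs f2 of about 0.080 at N = 100, or N = 107. That small gap is a separate matter; 0.080 is used below as the reference for model (1).

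**Why adjusted R-squared is a weak screen.** Adjusted R-squared = 1 - [RSS/(n - k - 1)] / [TSS/(n - 1)], with k predictors. Adding one term raises it exactly when the residual mean square falls, that is, when the term has |t| > 1. For the first added term at n = 100 there are 96 residual df and P(|t| > 1) = 0.32 with no effect. A useless term therefore passes about one time in three.

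**Simulation with no treatment effect.**

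From the plan: 1:1 allocation, n = 100 (or 70 after 30% dropout), models (1) and (2), a two-sided test.

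Assumed:
- 5% level.
- Any rise in adjusted R-squared justifies the larger model.
- Terms enter in the order Treatment x WAZpre, WAZpre cubed, Treatment x WAZpre cubed, which gives four models.
- Normal baseline WAZ with mean from -2.5 to 0 and SD 1 to 2, and residual SD 0.3 to 0.5.
- A linear baseline relation, with one mildly cubic setting.

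Each setting used 4,000 to 10,000 trials. At a true rate of 10% and 6,000 trials the simulation standard error is sqrt(0.1 x 0.9/6000) = 0.4 points.

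| Test made in the reported model | Stop at first non-improvement | Best of the four |
|---|---|---|
| Joint F-test of all treatment terms | about 7-8% | about 9% |
| Any treatment term p < 0.05 | about 10-12% | about 15-17% (13.4% in the mildly cubic setting) |
| A model beyond (1) is selected (linear baseline relation) | 31-33% | 53-54% |

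Relative to 5%, the joint test is at 7/5 = 1.4 to 9/5 = 1.8 times nominal. The any-term rule is at 10/5 = 2.0 to 12/5 = 2.4 times with stopping, and 15/5 = 3.0 to 17/5 = 3.4 times with best of four.

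Testing only b1 in the selected model gave 4.6% to 8.9% with stopping. In a model with interactions, however, b1 is the effect at WAZ = 0, where section 4 expects no change.

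**Control.** With the test fixed in advance, Treatment in model (1) rejected in 4.4% to 5.5% of trials, and the 3-df joint test in model (2) in 4.7% to 5.9%. The excess comes from the selection and from the choice among terms.

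**The case against.** Several objections have force.

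- **No any-term success rule is written.** Section 4 links each form of effect to a pattern of baseline WAZ. It does not say that one significant term among several is enough. A reader might infer a false-positive rate of two to three times nominal as a fact; the document invites the any-term reading but does not fix it. This stands, and the size must be given by reading.
- **Stepwise stopping is the more natural reading** of an assessment made at each step. The 15-17% needs the best-of-four reading and the any-term rule together. This also stands, although reporting the best fitting model leaves both stopping rules open.
- **No threshold is given for adjusted R-squared.** The one-in-three figure assumes that any rise suffices.
- **Nothing says the other models will be withheld.** A reader might infer this, but the text says only which model's results will be reported.
- **The candidate set is short, listed in advance and motivated by a hypothesis, and the analyst is blinded.** This limits ad hoc choice. It does not remove the inflation, because the coded groups still enter the selection.
- **The form depends on baseline WAZ.** A choice made from baseline values alone would be harmless. Adjusted R-squared instead measures fit to final WAZ.
- **A statistical analysis plan may settle it.** The protocol itself prescribes the data-driven rule, so this is not detail left for later, and an analysis plan that followed it would carry the same fault.

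**Conclusion.** The point holds, with its size conditional on the reading. The stated procedure selects the primary model on outcome data and fixes no primary test, and under the assumptions listed the false-positive rate exceeds 5% for the joint test and for the any-term rule: about 7-9%, 10-12% or 15-17%, as tabulated. The 5% level, the any-rise rule and the baseline and residual distributions are assumptions; the results moved little across the ranges tried.

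A reader might also infer that reverting to model (1) would cost nothing. The plan's own hypothesis does not support that. Section 4 and Fig. 2 anticipate gains in underweight children, reductions in overweight children and no change between. If baseline WAZ spans both tails, the average effect is close to zero. With baseline mean 0, SD 1.5, residual SD 0.4 and n = 100, an assumed effect of -0.1 x WAZpre gave model (1) about 5% power against 32-35% for a 2-df joint test. An assumed effect of -0.02 x WAZpre cubed gave 4-5% against 52-54%.

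**What to change.** Before unblinding, name one primary model and one primary test: a joint F-test, at a stated two-sided level, that all treatment terms in that model are zero. Two suitable choices are Treatment with Treatment x WAZpre (2 df), or model (2) with b1 = b3 = b5 = 0 (3 df), which keeps the cubic hypothesis. Report the test whatever the fit, with treatment effects and confidence intervals at stated baseline values such as WAZ -2, 0 and +2. Label the adjusted R-squared sequence exploratory.

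The change is to wording only, but it costs some sensitivity. With noncentrality f2 x 100 and a 5% level, the f2 detectable with 80% power at n = 100 is about 0.080 for the 1-df test (97 residual df), 0.099 for the 2-df test (96 df) and 0.114 for the 3-df test (94 df).

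Fixing model (1) alone also restores the error rate and matches the basis of the sample size. It should be chosen only if the sponsor expects baseline WAZ to lie mainly at one end, because it has almost no power against effects of opposite sign in the two tails.

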### Sample size calculation

4.1

Sample size calculations are based on assuming that 1) is the best fitting model. While it is desirable to base sample size on the most complex model used in the analyses, given that 1) it is unclear which model will show best fit to the data, and 2) estimates of sample size for regression models including interactions require understanding of the correlations between the variables, an understanding that we currently do not have, this approach was deemed warranted.

Sample size calculations were conducted in G*Power 3.1 1 Fig. 3 shows the sample size calculations assuming that 1) the effect of the intervention will be small to medium, and 2) a two-sided significance test.

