#### Inclusion criteria

3.3.1

Children aged between 2 and 12 years who have been diagnosed with cerebral palsy by a qualified neurologist will be eligible for the study. The diagnosis of CP can refer to spastic, dyskinetic, ataxic, or mixed CP. Only children of families who intend to continue to reside in the catchment area for the duration of the study will be included.

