## Planned analyses

4

The outcomes of the intervention will be assessed using both Intention-to-Treat (ITT) and Per-Protocol (PP) approaches. In the ITT approach, analyses include all study participants who were randomized to either of the study arms. In the PP approach, the analyses are restricted to participants who adhere to the protocol. We will not perform any imputation for missing data. Typically, the ITT method is favored for trials aiming to demonstrate superiority or non-equivalence (such as our study), PP approach is more suitable for trials assessing equivalence or non-inferiority Ahn et al., [15]. Nonetheless, it is advisable to execute both methods of analysis and compare their outcomes to identify any notable discrepancies. Employing both the ITT and PP strategies offers a fuller understanding of the effects of the treatment and enhances the credibility of the trial findings. In the case of the ITT analysis, we will focus on Weight for age Z-score (WAZ) (based on WHO standards 2006–2007) [16]. As WAZ is a standardized score for an individual given population norms, we anticipate the intervention to produce change at the tails of the distribution (for children outside the normal range) rather than the center (children in the normal range). This suggests that, in the intervention group, the baseline WAZpre variable may have a cubic relationship with the outcome WAZpost variable (Fig. 2).

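### The stated 0.8 power applies only to an average shift in model (1); for the tails-only effect the plan expects, power depends on baseline WAZ and can be far lower

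*Protocol article*

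**What the plan says.** Section 4 (Planned analyses) sets out the hypothesis for weight-for-age Z-score (WAZ): "we anticipate the intervention to produce change at the tails of the distribution (for children outside the normal range) rather than the center". The caption of Fig. 2 describes "the intended change for underweight and overweight children and the intended no change for children with weight in the normal range". The text below it adds that the term carrying the effect depends on baseline WAZ. It is the main effect if children lie mostly at one end, Treatment × WAZpre if they run from one end to zero, and Treatment × WAZpre³ if they span the whole range. The model to report is chosen by adjusted R-squared, starting from model (1) (Treatment and WAZpre) and going up to model (2) (with interaction and cubic terms).

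Section 4.1 (Sample size calculation) says "Sample size calculations are based on assuming that 1) is the best fitting model". It concedes that using the most complex model would be preferable and gives two reasons for not doing so: the best-fitting model is not known in advance, and the correlations needed are unknown. The calculation used G*Power 3.1 and "a two-sided significance test". The result is a "total sample of 100 participants, which will allow us to detect effects as small as f2 = 0.075 with power of 0.8".

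Section 3.3.1 (Inclusion criteria) says "Children aged between 2 and 12 years who have been diagnosed with cerebral palsy by a qualified neurologist will be eligible for the study". Neither it nor section 3.3.2 (Exclusion criteria) lists a criterion on baseline weight or WAZ.

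**The concern.** In model (1) the treatment coefficient b1 is one shift averaged over all children. If normal-weight children are expected not to change, they dilute that average. If overweight children are expected to move down while underweight children move up, the two tails offset each other. Nothing in eligibility ensures that the sample lies at one end of the WAZ range, which is the case in which the plan itself expects a main effect.

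The 0.8 is the only power figure given in the text, and it applies to a form of effect that the plan does not expect in general. A reader would take it as the chance of detecting a working intervention.

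The meaning of b1 also changes with the model. Once Treatment × WAZpre enters, b1 is the effect at WAZpre = 0, the centre of the range, where the plan expects no effect. It should not then be read as the answer to the primary objective (section 2.1).

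**Working it through.** **Inputs from the article.** N = 100, 1:1 allocation (section 3.5), f2 = 0.075, two-sided test, model (1) with two predictors.

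**Assumptions.** The text gives no alpha (Fig. 3 is not shown), so 0.05 is assumed. The article gives no baseline WAZ distribution, so all means, SDs, cut-offs and tail shares below are assumed. Opposite directions in the two tails are inferred from the Fig. 2 caption and the cubic form, because the figure is not shown.

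**1. The plan's own figure.** For one coefficient, the noncentrality is √(f2 × N) = √7.5 = 2.74 on 100 − 3 = 97 df. Power is 0.774, not 0.80. At N = 100, 80% needs f2 = 0.080; at f2 = 0.075 it needs N = 107. This is a near miss.

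**2. What f2 = 0.075 means.** At 1:1 allocation, d = 2√f2 = 2 × 0.274 = 0.548 residual SD, averaged over all children.

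**3. Dilution and offset.** If underweight children shift by +0.548 SD, overweight children by −0.548 SD and the rest not at all, the average effect is (share low − share high) × 0.548. With 50 per arm and the normal approximation, power = Φ(5 × average effect − 1.96).

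| Share low / high | Average effect | Power | Total N for 80% |
|---|---|---|---|
| 100% / 0% | 0.548 | 0.78 | 106 |
| 75% / 0% | 0.411 | 0.54 | 188 |
| 50% / 0% | 0.274 | 0.28 | 420 |
| 40% / 10% | 0.164 | 0.13 | 1164 |
| equal tails | 0 | about alpha | none suffices |

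Conversely, if f2 = 0.075 is read as the already diluted average and only one tail is present, the effect in affected children must be 0.548/q for an affected share q. That is 1.1 SD at q = 0.5 and 1.8 SD at q = 0.3.

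**4. Simulation.** N = 100, baseline WAZ SD 1.5, residual SD 1. The effect is a step towards normal for children beyond ±1 and zero between. Model (1) is the t-test of b1; the joint test is the 2-df F-test of Treatment and Treatment × WAZpre.

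| Effect beyond ±1 | Baseline mean | Model (1) | 2-df joint test |
|---|---|---|---|
| 0.55 SD | −2 | 0.49 | 0.47 |
| 0.55 SD | −1 | 0.20 | 0.37 |
| 0.55 SD | 0 | 0.05 | 0.29 |
| 1.1 SD | −2 | 0.96 | 0.97 |
| 1.1 SD | −1 | 0.55 | 0.92 |
| 1.1 SD | 0 | 0.05 | 0.86 |

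In these settings, b1 from the model with Treatment × WAZpre rejects in only about 5 to 11% of trials, as its meaning implies.

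Model (1) comes close to the stated power for a moderate effect only when nearly all children are underweight. With baseline mean −3, SD 1 and an effect of 0.566 SD (f2 = 0.08, which gives 0.80 if shared by all), power is 0.78 with the cut-off at ±1, where 98% of children are affected. With the cut-off at ±2, where 84% are affected, it is 0.65.

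**5. Detectable effect of the 2-df test.** From the noncentral F with noncentrality f2 × N, 80% power needs f2 = 0.099 at n = 100 and 0.144 at n = 70. Under a uniform shift with f2 = 0.075 at n = 100, its power is 0.67.

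**The case against.** A reader might infer that the trial's test is nearly blind to the hypothesised effect. The documents do not support that in general. It holds only if the two tails roughly balance or few children are outside the normal range. The Introduction, section 3.8.2 and the Discussion present malnutrition as common in cerebral palsy, so a skew to low weight is plausible. Model (1) is then underpowered for a moderate effect but can be adequate for a large one (0.96 at mean −2 with 1.1 SD).

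A reader might also infer that the plan will report a null b1 although the intervention works. Section 4 does not make b1 the test whatever the model. It says that an interaction may carry the effect and that the best-fitting model is reported. In simulation, adjusted R-squared kept model (1) in at most 8% of runs with a 1.1 SD effect and in 16 to 29% with 0.55 SD, so cancellation in model (1) would often not be the reported result. The same fact shows that the powered model is often not the one reported. The article does not say which coefficient or joint test then answers the primary objective.

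Nor does the sample size flatly contradict the hypothesis. The f2 is given as a detectable effect, and read as an average it is compatible with a tails-only effect. The simplification is disclosed, with two reasons. Those reasons do not prevent showing power over several assumed baseline distributions, and the article nowhere says that 0.8 depends on that distribution.

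Two further objections stand. Every size above rests on assumed baseline inputs. The joint test also gains nothing over model (1) at mean −2 with a 0.55 SD effect.

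**Conclusion.** The point holds in a limited form. The 0.8 applies to an average shift in model (1) and is about 0.77 at the stated f2 and N. Under the plan's own tails-only hypothesis, with 0.55 residual SD in affected children, model (1) power runs from about 0.05 to 0.49 across baseline means 0 to −2, and approaches the stated figure only if nearly all children are underweight. This rests on two-sided alpha 0.05, opposite directions in the two tails, and assumed baseline distributions (SD 1.5, step effect beyond ±1). The direction of the finding follows from the article's own text; the size does not. The weakness is that an acknowledged simplification is reported without its consequence, and that b1 loses its meaning as an overall effect once an interaction enters. It does not show that the trial cannot detect a working intervention. The change should be made, because the article gives no other power figure in its text and the correction is cheap.

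**What to change.** 1. Restate the power paragraph in section 4.1. Say that the figure is for an average shift only: about 0.77 at f2 = 0.075, or 80% at f2 = 0.080, with n = 100 and the alpha named. Add power, or the detectable effect in children outside the normal range, for several assumed baseline WAZ distributions or affected shares.

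2. Prespecify one joint test of all treatment terms as the primary test, in place of a test from whichever model adjusted R-squared selects. An example is the 2-df test of Treatment and Treatment × WAZpre, with detectable f2 0.099 at n = 100 and 0.144 at n = 70. It leaves out the cubic interaction. If the team regards that term as essential, the 3-df version is the alternative, and its power should be shown as well.

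3. Report the treatment effect averaged over the baseline distribution and at stated WAZ values, and do not present b1 from an interaction model as the overall effect.

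**Cost.** Only analysis and sample-size wording changes. The 2-df test gives up about 10 points of power if the true effect is a uniform shift (0.77 to 0.67). It also loses some power if nearly all children are underweight: from a little over 0.6 to about 0.55 with mean −3, SD 1 and 0.55 SD beyond ±2. It does not make a 0.55 SD tails-only effect well powered (0.29 to 0.47 in the table), and the restated paragraph should say so.
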